#### **4.3.6 Laboratory Parameters**

Clinical chemistry, hematology, serology, and steroid will be performed by a qualified central laboratory in the Netherlands. At the research site in Almere the total amount of blood to be drawn during this study is 47 ml (21 ml at screening, 16 ml at follow up, and 15 ml for assessment of genetic markers). Because of a different laboratory where the blood from the research site in Utrecht will be analysed, the total amount to be drawn in Utrecht is 65,5 ml (34,5 ml at screening, 16 ml at follow up, and 15 ml).

Urine drug screen, routine urinalysis (as listed below), and urine pregnancy testing will be performed at the clinical sites.

Each parameter outside the normal range will be designated as high or low on the laboratory documentation. The investigator will determine if "outside the normal range" values are clinically relevant; if so, an assessment will be provided.

##### **4.3.6.1 Urine Drug Screening**

A fresh urine sample (10-20 mL) will be collected for urinary drug screening. Urinary drug screening for amphetamines, barbiturates, benzodiazepines, cocaine, methamphetamines, MDMA, morphine, methadone, tricyclic antidepressants and THC will be performed qualitatively at the screening visit (V0).

#### **4.3.6.2 Urinalysis**

During screening (V0), a fresh urine sample (20 mL) will be collected and analyzed with a dipstick for bilirubin, blood, glucose, ketones, pH, protein, specific gravity, urobilinogen, leukocytes, and nitrite.

For each parameter testing +, the investigator will determine if the results are clinically relevant; if so, an assessment will be provided.

#### **4.3.6.3 Urine Pregnancy Test**

A test for urinary human chorionic gonadotropin will be done at each visit to the site for women of child-bearing capability.

#### **4.3.6.4 Hematology and Blood Chemistry**

Blood samples will be collected for hematology and blood chemistry safety assessments at the screening visit (V0) and at the final follow up visit (V6). See Appendix 3 for a list of assessments performed at each of these visits. For potential subjects who exceed the 12 week window between V0 and V1 and who continue to be eligible for inclusion, hematology, chemistry and hormone levels will be drawn.

#### **4.3.6.5 Luteinizing Hormone, Follicle Stimulating Hormone, Sex Steroids, Sex Hormone Binding Globulin, and Prolactin**

Blood samples will be collected at screening (V0) to determine levels of the following: total testosterone, sex hormone binding globulin (SHBG), estradiol, luteinizing hormone, follicle stimulating hormone, and prolactin. Total testosterone and SHBG will also be determined at the final follow-up visits (V6).

#### **4.3.6.6 Serology**

Assessment of hepatitis B surface antigen, hepatitis C antibody, and HIV antibodies for HIV-1 and HIV-2 will be performed at screening (V0).

#### **4.3.6.7 Biological markers**

A blood sample will be collected at the start-up visit (V1) after randomization.

#### **4.3.7 Safety and Tolerability Measurements Procedure**

All subjects will be part of the safety and tolerability evaluation. Subjects will be monitored for vital signs, AEs, hematology, and blood chemistry during the study and on follow-up.

#### **4.3.8 Safety Assessments**

##### **4.3.8.1 Vital Signs**

Vital signs will be measured at all visits. Systolic blood pressure and diastolic blood pressure will be taken with the subject in a supine position for at least 5 minutes. For subjects whose initial BP reading is outside the specified acceptable range, one to two subsequent readings should be obtained. Two successive out-of-range readings disqualify subjects from participation. Heart rate

will also be measured. Subjects should be observed closely for any sign or report of dizziness or lightheadedness upon standing.

#### **4.3.8.2 Hyperandrogenism Monitoring**

Monitoring for the following signs of hyperandrogenism will be performed at all visits: hirsutism (terminal hair on the lip, chin, chest, abdomen, and back); acne; seborrhea; temporal balding; acanthosis nigricans; striae; thin skin or bruising; deepening of the voice; frontal (or crown) balding; increased muscle mass; or clitoromegaly (if reported by subject, length > 10 mm and/or index > 35 mm^2 is considered above normal).

If a subject reports one or more of the above symptoms, an extra blood sample will be collected to determine the serum total testosterone, SHBG, albumin level and calculated free testosterone. See Section 4.4.2 for study stopping rules regarding hyperandrogenism.

#### **4.3.8.3 Electrocardiogram**

A 12-lead ECG with a hard-copy output will be taken at the screening visit (V0). The screening ECG will be evaluated by the medical investigator. Heart rate, PR interval, QRS duration, QT interval, QTc interval (Bazett), and any abnormalities will be recorded. The Investigator/qualified designee will initial and date the copy to indicate agreement with tracing analysis or will re-interpret, initial and date.

#### **4.3.8.4 Physical Examination**

The physical examination performed at the screening visit (V0) will constitute the baseline measurement for the study period.

#### **4.3.9 Adverse Events**

Information on AEs will be gathered by spontaneous reporting in the weekly diary and at all visits to the site.

#### **4.3.10 Food and Beverages**

Moderate use of alcohol is allowed.

### **4.4 Study Termination**

#### **4.4.1 Regular Study Termination**

The final follow-up visit (V6) is also the end-of-study visit. This visit will be scheduled to occur 1 week after the last study regimen follow-up visit (V5). A full safety assessment will be conducted (see Section 4.3.2.4 for details).

#### **4.4.2 Premature Study Termination**

Subjects may be withdrawn from the study for any of the following reasons:

1. At their own request, or at the request of their legally authorized representative

2. If, in the investigator's opinion, continuation in the study would be detrimental to the subject's well being
3. A significant protocol violation
4. Severe laboratory abnormality where continuation of participation could put the subject at risk
5. Hyperandrogenism, defined as one or more reported signs of hyperandrogenism (see Section 4.2.9.2) in combination with serum total testosterone levels or calculated free testosterone above the normal range
6. A subject who develops new angina or significant cardiovascular disease should be terminated from the study to avoid the potential emergency intake of nitrate therapy in close association with the intake of study medication
7. The treatment code is broken
8. The subject becomes pregnant
9. There is a change in partner availability (through termination of the relationship, travel, or other circumstances that remove the partner for an extended period of time)

Subjects who experience an intolerable AE or who become pregnant will be withdrawn from study treatment but will continue to be monitored until the AE has resolved or the outcome of the pregnancy has been determined.

When a subject terminates between Visit 1 and Visit 6, she should be asked to return to site for a safety blood draw (Chemistry, Hematology and Hormone) and documentation of any significant changes from her baseline assessments, AEs and/or SAEs.

#### **4.5 Breaking the Blind**

The blind may be broken for a subject only in exceptional circumstances. The only acceptable reason for requesting to break the blind by the investigator is that the information is necessary for medical management of the subject. The investigator must, whenever possible, contact the sponsor's Medical Monitor to provide details on the reason for wanting to break the code. If approved, the Medical Monitor will unblind the subject and reveal the randomization code to the inquiring investigator. This notification must include the appropriate documentation, signed and dated by the investigator and giving the reason for breaking the code. All further procedures undertaken with respect to circumstances related to breaking the blind must be confirmed in writing within 3 working days after breaking the blind. Subjects whose code has been broken must be discontinued from the clinical trial, and the reason for discontinuation must be documented.

The sponsor, together with the investigator and the responsible statistician (if applicable) will determine the implications for analysis of data from the subject. Appropriate documentation must be completed, signed, and dated by the responsible clinical project manager.

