## 4 STUDY ACTIVITIES AND EVALUATION METHODS

### 4.1.1 Study Medication & Route of Administration

#### *Lybrido*

Lybrido is a fixed-dose combination of testosterone and sildenafil citrate. The drug product is a 9 mm, round, biconvex, white, menthol-flavored tablet for sublingual administration. The outer, polymeric, film coating contains testosterone (0.5 mg) that is released immediately after sublingual administration. The inner core of the tablet contains sildenafil (50 mg). This inner core has a polymeric coating designed to delay release of the sildenafil for approximately 2.5 hours; after this time delay, the sildenafil is released immediately (i.e., it is not a sustained release).

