#### *Placebo*

The placebo has the exact same appearance and flavor as Lybrido and Lybridos.

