#### **4.2 Enrollment and randomization**

Subjects will be enrolled after meeting the inclusion/exclusion criteria and within 12 weeks after screening (V0) (before Visit 1). Thereafter they complete a 2-week single blind placebo regime. Up until visit 2, subjects will only receive placebo (run in period). However, since all medication is packed into a single kit, subjects will be randomized prior to V1. The placebo run-in period is followed by a double blind 6-week treatment period. This treatment period consists of a 2-week Lybrido, a 2-week Lybridos, and a 2-week placebo regime. Each subject completes the treatment regime in a randomized order. The randomization schedule follows a Williams design with 6 sequences. The list with the randomized medication kit-numbers will be designed by an independent statistician. Subjects will be randomized, at least 24 hours before V1, using the electronic CRF. One of the unique medication code numbers from the randomization schedule will be coupled with the randomized subject.

A subject identification code will be used to keep the data anonymous. The code will consist of a 2-digit site code, a 4-digit subject screening number and a 3-digit randomization number (e.g., 01-0123-001). Access to the key for the code (subject identification log) will be restricted and safeguarded by the Medical Monitor. If a subject discontinues from the study, the unique subject identification code will not be used again.

In alignment with the intention-to-treat analysis, subjects who have received study medication will not be replaced. A subject will be replaced if she has not yet received any study medication (e.g., the subject decides to stop before V1) but only during the enrolment period (a duration of 16 weeks) of the study. When the enrolment period has ceased, subjects will not be enrolled or replaced.

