Medical and scientific judgment should be exercised in deciding whether expedited reporting is appropriate in other situations, such as important medical events that may not be immediately life-threatening or result in death or hospitalization, but may jeopardize the patient or may require intervention to prevent one of the other outcomes listed in the definition above. These should also usually be considered serious. Also serious events which could be associated with the trial procedures (rather than with the IP) will be reported as SAEs, even if occurring outside the treatment procedure.

Under this protocol, the following event(s) will not be considered as (an) SAE(s) and should not be entered on the SAE form:

Pre-planned hospitalizations for diagnostic, therapeutic, or surgical procedures for a pre-existing condition that did not worsen during the course of a clinical trial. These pre-planned hospitalizations must be entered on the medical history form, including the condition requiring hospitalization. These events will, if applicable, still be reported as an AE.

Companion Diagnostic BV or its representatives will report all Suspected Unexpected Serious Adverse Reactions (SUSAR: SAEs that are unlisted and associated with the use of the drug) to the investigators, the Independent Ethics Committee (BEBO), the regulatory authorities (CCMO), and the CBG (College ter Beoordeling van Geneesmiddelen) within 24 hours.

The SUSAR report will contain the following information:

- the Eudract number of the study and the sponsors protocol study name and study number in which the SUSAR has taken place;
- the identification number which the investigator has given the SUSAR;
- the name and address of the person whom has reported the SUSAR;
- a description of why the SUSAR is suspect;
- a description of the study trial medication which suspectedly caused the SUSAR;
- the subjectcode, age and gender of the subject whom has had –or is having- the SUSAR;
- a description of the SUSAR, of it's course/the course of events, and a description of the treatment thereof/ the action taken;
- an assessment of the (consequences of) the SUSAR by the investigator for the (ongoing) clinical study;
- any other relevant information regarding the SUSAR.

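### Section 4.5 describes no means for the investigator to obtain the treatment code for medical management if the sponsor's Medical Monitor cannot be reached or does not approve

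*Protocol*

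**What the plan says.** Section 4.5 of the protocol limits code breaks to exceptional circumstances and gives one ground for them: "The only acceptable reason for requesting to break the blind by the investigator is that the information is necessary for medical management of the subject". It then sets out the procedure. The first step is "The investigator must, whenever possible, contact the sponsor's Medical Monitor to provide details on the reason for wanting to break the code". The second is "If approved, the Medical Monitor will unblind the subject and reveal the randomization code to the inquiring investigator". The section adds requirements for signed documentation of the reason, for written confirmation within 3 working days, and for discontinuation of any subject whose code has been broken.

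Four other places bear on this:

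- Section 4.2: an independent statistician designs the list of kit numbers, and "Subjects will be randomized, at least 24 hours before V1, using the electronic CRF". No code-break function is given to that system.
- Section 4.1.1: the Lybrido tablet contains 50 mg sildenafil, and "The placebo has the exact same appearance and flavor as Lybrido and Lybridos". Each regimen supplies 8 tablets. At least 4 must be taken, the rest may be taken on demand, and dosing is permitted every day.
- Section 2.2.1 places the use of the drugs in the domestic setting.
- Section 4.4.2, item 6: a subject with new angina or significant cardiovascular disease leaves the study "to avoid the potential emergency intake of nitrate therapy in close association with the intake of study medication".

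**The concern.** Section 4.5 accepts that treatment information can be necessary for a woman's care, yet makes its release depend on a third party being available and agreeing. An investigator who follows the text exactly has nothing to do next if the Medical Monitor does not answer or does not approve.

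The design makes this more than a formality. Dosing happens away from the site, at times the woman chooses, so an event need not fall in working hours. The three double-blind regimens cannot be told apart by looking at the tablet. The protocol itself foresees one emergency, nitrate therapy close to a dose, for which what the woman has taken is relevant. At stake is how quickly, and whether, the treating physician can learn that. The efficacy analysis is not at stake.

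**Working it through.** The protocol gives no figure to reproduce. The check is whether any stated step covers each situation that section 4.5 can lead to.

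**Cases under section 4.5**

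| Situation | What the text provides |
|---|---|
| Medical Monitor reached, approves | The Medical Monitor unblinds and passes on the code |
| Medical Monitor reached, does not approve | No step stated |
| Medical Monitor not reached | The qualifier excuses the call; nobody else is named who can unblind |

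The qualifier attaches to the duty to make contact. The sentence on unblinding that follows has the Medical Monitor as its only actor and is conditional on approval. Excusing the call therefore does not supply the code.

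**Is a route given elsewhere in the protocol?** The relevant sections are:

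- 4.1.1 (products and dosing): indistinguishable tablets; no code-break provision.
- 4.1.2 (labelling): labels carry a kit number, a description of contents and sponsor contact information. In a double-blind trial the description cannot be read as naming the regimen, so the label helps to reach the sponsor but does not reveal the treatment.
- 4.2 (randomisation): the electronic CRF couples a kit to a subject. The Medical Monitor safeguards the subject identification log, which is the identity key and not the treatment code. No sealed codes or emergency function are described.
- 4.4.2 (withdrawal): item 7 lists a broken code as a reason for withdrawal, without saying how it is broken.
- 5.3 (safety reporting): reporting duties and deadlines, but no code access for the investigator.
- 7.4 (accountability): inventory and electronic monitoring of intake. This can show when a bottle was used, not what it held.

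None of these fills the second or third row of the table.

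**How often the code would be uncertain.** Three treatments can be ordered in 3! = 6 ways, which matches the six sequences of the Williams design. In any one period each treatment appears in 6 / 3 = 2 sequences. With equal allocation to sequences:

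- P(sildenafil product) = 2/6 = 1/3
- P(buspirone product) = 2/6 = 1/3
- P(placebo) = 2/6 = 1/3

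**Exposure over the trial**, if all of the approximately 150 women complete the three periods and comply:

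- Double-blind home dosing: 150 × 3 periods × 2 weeks = 900 woman-weeks.
- Sildenafil-containing tablets taken: from 150 × 4 = 600 to 150 × 8 = 1,200.

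These figures describe how much blinded dosing the procedure has to cover. They do not estimate how often a code break would be needed, for which the protocol gives no basis.

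**The case against.** The strongest reply is that the protocol does not make prior contact absolute, and that nothing in it says approval would be refused where medical management requires the code. That is right as far as it goes. A reader might infer that the investigator is barred from finding out directly, and the text does not go that far. What it supports is that no direct means is described. The gap remains, because the protocol admits that contact can fail and does not say what happens then.

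A second reply is that the mechanics may sit elsewhere. The contents list shows a section 5.4 with further contact information, which is not in the public text, and a medication or electronic CRF manual may exist. A round-the-clock contact would make the third situation in the table rarer. It would not remove the approval condition, and section 4.5 points to no other procedure.

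Third, item 6 of section 4.4.2 is a withdrawal rule. It does not describe an unblinding scenario or name sildenafil, so a reader should not take it as stating that emergency care turns on the code. Exclusion criterion 1 also removes cardiovascular conditions that would preclude sexual activity, so such an event should be uncommon. Both points stand. The item is used here only to show that the protocol foresees an emergency close to dosing. A rule that withdraws a woman once a condition has developed does not cover its first presentation.

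A reader might also infer that safety reporting lacks a permitted unblinding path, since section 5.3 asks for "a description of the study trial medication which suspectedly caused the SUSAR" within 24 hours. The documents do not support this. The restriction in section 4.5 is on requests by the investigator. Nothing bars the sponsor or its pharmacovigilance officer from unblinding, and the Medical Monitor who holds that power is the sponsor's own. Nor does the protocol say how long a direct code break would take, so no time saving can be claimed.

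**Conclusion.** The point holds in limited form. Section 4.5 recognises a medical need for the code, makes its release conditional on sponsor approval and action, and leaves two of the three situations it can lead to without a step. This is a defect in a stated safety procedure, and not a detail that a protocol would leave to a statistical analysis plan.

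Its size cannot be put as a risk. What can be said is that it applies throughout three 2-week double-blind periods per woman, in each of which the chance of holding the sildenafil product is 1 in 3. The conclusion rests on three assumptions: equal allocation to the six sequences (for the 1 in 3 only), no separate code-break procedure outside the protocol, and the inference that the nitrate emergency in section 4.4.2 is one where the code would be wanted. If a separate procedure exists, section 4.5 still needs correcting, because its wording makes approval a condition. It should be amended; the change does not bear on the validity of the primary analysis.

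**What to change.** Amend section 4.5 to state that:

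1. The investigator can obtain the treatment code directly and at any hour when it is needed for a subject's medical management. Suitable vehicles are a logged code-break role in the electronic CRF already used for randomisation, or sealed codes held at each site.
2. The Medical Monitor is contacted beforehand where possible and otherwise notified afterwards. Approval is not a condition.
3. The existing requirements stay: signed reasons and written confirmation within 3 working days.

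If a code-break procedure already exists in another document, section 4.5 should refer to it and be made consistent with it. No dose, treatment or withdrawal rule needs to change.

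The cost is protocol wording plus an access role or a set of sealed codes at up to two sites. The downside is a slightly greater chance of an unnecessary code break. Any such break would be logged, and the documentation and discontinuation rules already in section 4.5 discourage it.

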#### **4.6 Interim Database Lock**

This study will have one interim database lock. This interim database lock will take place on the first 75 subjects with FSIAD who complete the study. This is done so that on these subjects an altered/improved demarcation formula can be based. The data of the second set of 75 subjects with FSIAD who complete the study will be used to validate this altered demarcation formula.

## **5 ADVERSE EVENTS AND SERIOUS ADVERSE EVENTS**

### **5.1 Definitions**

An AE is defined as any undesirable effect experienced by a subject during a clinical study, whether or not considered related to the investigational product and/or the experimental treatment. All AEs reported spontaneously by the subject or observed by the investigator or his/her staff will be recorded. The assessment for AEs will begin with Visit 1 and end at the completion of Visit 6.

A serious adverse event (SAE) is any untoward medical occurrence or effect that at any dose:

- results in death;
- is life threatening (at the time of the event);
- requires hospitalization or prolongation of existing inpatient's hospitalization;
- results in persistent or significant disability or incapacity;
- is a congenital anomaly or birth defect;
- is a new event of the trial likely to affect the safety of the subjects, such as an unexpected outcome of an adverse reaction, lack of efficacy of an investigational product used for the treatment of a life threatening disease, major safety finding from a newly completed animal study, etc.

Note: The term "life-threatening" refers to an event in which the patient was at risk of death at the time of the event; it does not refer to an event which hypothetically might have caused death if it were more severe.

A suspected unexpected serious adverse reaction (SUSAR) is an SAE that is unlisted and associated with the use of the drug.

